## Abstract

**Background:**

Up to 8% of all children in industrialized countries suffer from food allergies, whereas children with atopic eczema are affected considerably more frequently. In addition, the type and starting time of weaning foods seem to influence the development of food allergies. However, data from interventional studies on weaning are controversial.

The aim of this randomized-controlled clinical trial is to investigate, whether an early introduction of hen's egg (HE), cow’s milk (CM), peanut (PN), and hazelnut (HN) in children with atopic eczema can reduce the risk for developing food allergies in the first year of life.

**Methods:**

This is a protocol for a randomized, placebo controlled, double blind, single-center clinical trial.

One hundred fifty infants with atopic eczema at 4–8 months of age will be randomized in a 2:1 manner into an active group that will receive rusk-like biscuit powder with HE, CM, PN, and HN (initially approximately 2 mg of each food protein) for 6–8 months or a placebo group, whose participants will receive the same rusk-like biscuit powder without HE, CM, PN, and HN on a daily basis. During the interventional period, the amount of allergens in the study product will be increased three times, each after 6 weeks. All study participants who are sensitized to HE, CM, PN, or HN at the end of the interventional period will undergo an oral food challenge to the respective food in a further visit.

Primary endpoint is IgE-mediated food allergy to at least one of the four foods (HE, CM, PN or HN) after 6–8 months of intervention (i.e., at around 1 year of age). Secondary endpoints include multiple food allergies, severity of eczema, wheezing, and sensitization levels against food allergens.

**Discussion:**

This clinical trial will assess whether an early introduction of allergenic foods into the diet of children with atopic eczema can prevent the development of food allergies. This trial will contribute to update food allergy prevention guidelines.

**Trial registration:**

German Clinical Trials Register DRKS00016770. Registered on 09 January 2020.

**Supplementary Information:**

The online version contains supplementary material available at 10.1186/s13063-022-06126-x.

## Background

IgE-mediated food allergy is a burden in industrialized countries with up to 8% of all infants and children suffering from this condition [1]. Especially infants with eczema are at high risk for developing food allergies [2]. About half of these children become sensitized and about one third will develop clinically relevant food allergy [1, 3, 4]. The main elicitors are HE, CM, PN and tree nuts. Food allergy often starts in infancy and interestingly the children become sensitized against certain foods even before eating them for the first time. It is the current understanding that sensitization occurs via the cutaneous route due to an impaired skin barrier function in these infants [2]. In the past, prevention strategies concerning the development of food allergy have been driven by avoidance of allergenic foods in high-risk infants. Despite these attempts, a rising prevalence of food allergy has been observed [1, 5]. Therefore, current guidelines no longer recommend avoidance [6, 7]. However, the optimal way of allergen introduction into the infants´ diet is still under debate. The main questions are “when,” “how,” “which allergen,” and “which children.”

To address these questions, several randomized controlled studies have been conducted with different foods [8–14]. The LEAP trial in the UK focused on peanut allergy in high-risk children (severe eczema and/or hen’s egg allergy) [8]. After randomization, 540 participants from 4 to 11 months of age were asked to consume peanut three times weekly or to avoid peanut strictly until the age of 5 years. In this high risk population, early and continuous feeding of peanut products reduced the development of peanut allergy by 80% [8]. However, it is still unclear how these results can be transferred to other countries where peanuts are less frequently consumed. For instance, data from Singapore showed very low prevalence rates of peanut allergy despite the fact that peanuts are not introduced into infants’ diets in the first year of life [9].

Regarding HE, five intervention studies showed no clear reduction of allergy but high rates of adverse reactions, both immediate type symptoms and gastrointestinal problems [10–12]. However, one small study from Japan showed a significant reduction of hen’s egg allergy without adverse events. In contrast to the other prevention studies, they started with very small amounts of heated egg powder, increasing to small amounts after 3 months. One hundred twenty-one infants were enrolled at 4–5 months of age with two thirds of the infants being already sensitized to hen’s egg with unknown clinical relevance. At 12 months of age, only 8% of the active group versus 38% of the placebo group had developed hen’s egg allergy [13].

Many children develop food allergy to more than one allergen and prevention strategies should keep this in mind. Another randomized but not placebo-controlled trial in the UK, the EAT study, focused on the effects of the early administration of various foods to breast-fed infants from the general population [14]. From a total of 1303 children, in an intervention group, six different allergenic foods were introduced into their diet, starting at 3 months of age (early introduction group), while the standard introduction group was exclusively breast-fed until 6 months of age. In the per-protocol analysis, the prevalence of any food allergy was significantly lower in the early introduction group than in the standard introduction group (2.4% versus 7.3%). However, in the intention-to-treat-analysis, there was no statistically significant difference between both groups (5.6% versus 7.1%), because in the majority of infants, the protocol was not followed [14]. Reasons for this might be the complicated protocol of consecutive food introduction, or adverse reactions.

In conclusion, further research is needed before evidence-based advice can be given for the prevention of food allergy.

Therefore, we will introduce small amounts of four highly allergenic foods (baked HE, CM, PN, and HN) together in infants with eczema at 4–8 months of age in a randomized, placebo-controlled, clinical trial in order to assess oral tolerance development. This is an abridged protocol based on protocol version 4.0 dated 05 April 2021. The full protocol is available on: German clinical trials register http://www.drks.de (DRKS00016770 or https://www.drks.de/drks_web/navigate.do?navigationId=trial.HTML&TRIAL_ID=DRKS00016770).

This protocol adheres to the Standard Protocol Items: Recommendations for Interventional Trials (SPIRIT) recommendations for interventional trials and the SPIRIT Checklist is included (see Additional file 1) [15].

## Methods

### Objectives

The primary objective is to assess the efficacy (superiority) of an early introduction of small amounts of allergenic foods on the development of food allergy in the first year of life in infants with eczema. Secondary objectives are to investigate if an early introduction of small amounts of allergenic foods in the first year of life is safe or if it results in the occurrence of allergic reactions, gastrointestinal problems, or in failure to thrive. Moreover, the impact of an early introduction of small amounts of allergenic foods on the development of multiple food allergies, severity of eczema, the prevalence of asthma, and distinct immunoglobulin pattern in the first year of life will be assessed.

### Trial design

Tolerance induction through Early Feeding to prevent Food Allergy in infants with eczema (TEFFA) is a randomized, placebo controlled, double blind, single center trial with two parallel groups (Fig. 1). All study participants who are sensitized to HE, CM, PN, or HN at the end of the interventional period will undergo an oral food challenge (OFC) to the respective food after 6–8 months.

**Fig. 1 Fig1:**
[figure not shown]
Study design overview. The diagram shows the flow of the patients after enrolment and randomization in the active or the placebo group. Subjects in the active group will receive a sugar-free rusk-like biscuit powder with hen´s egg, cow’s milk, peanut, and hazelnut, while subjects in the placebo group will receive a sugar-free rusk-like biscuit powder without these allergens. After 6 months of intervention, we will check for sensitization against hen’s egg, cow’s milk, hazelnut, and peanut. All sensitized subjects will receive the study product until they will undergo an oral food challenge against the corresponding foods, while in the non-sensitized infants the intervention will be stopped

TEFFA is part of the clinical research unit (CRU) 339 “food allergy and tolerance” (FOOD@). Using biological samples obtained within the trial, several mechanistic sub-projects will be performed in order to gain a deeper understanding of the immunological mechanisms involved in food allergy and tolerance development. In particular, the role of the gastrointestinal as well as the skin microbiome, the IgEome, epigenetic mechanisms, antigen specific immunologic reactivities as well as inflammatory circuits, and serological biomarkers will be investigated. The methods of these sub-projects will be described elsewhere.

### Setting

This single-center trial is recruiting participants at the Charité - Universitätsmedizin and at regular well-baby check-ups at primary care physicians in Berlin. Additionally, we aim to approach participants via flyer advertisement, advertisement in journals, magazines, and social media as well as at information events for (prospective) parents. All visits throughout the study will take place either in the study center (V1-V5) or on ward (V6: DBPCFC).

### Participants

Infants with eczema 4–8 months of age are eligible for the trial. Eczema is defined as doctor´s diagnosed or parent-reported doctor´s diagnosed and will be finally evaluated by the study physician according to the criteria of Hanifin and Rajka [16]. Infants are excluded from the study if they have previously consumed HE, PN, or HN. Previous consumption of CM is no exclusion criterion, since infant formula commonly is based on CM and formula fed infants should be also addressed. Further exclusion criteria are wheat allergy (study product contains wheat), health issue (cardiac or congenital), and participation in another interventional trial.

### Consent procedure

All legal representatives of the participants must read, sign, and date the informed consent form before entering the study or undergoing any study-specific procedures. Before consent is given, the investigator or his/her representative will explain verbally the aim, method, source of funding, and the anticipated benefits and potential risks of the study to the parents, answer all questions regarding the study, and document the informed consent process. As opt-it consent, included in the main study consent form, biological specimens are collected and partially stored for future analysis. A unique participant number will be allocated to each participant and assigned chronologically prior to proceeding with study screening. The sequential identification numbers rather than names will be used to collect, store, and report participant information.

### Intervention

In the active group, subjects consume a sugar-free, rusk-like biscuit powder daily, which contains small amounts of HE, CM, PN, and HN. The allergen doses in the study product will be approximately 2 mg of each food protein at 4–8 months of age and will be increased three times during the study every 6 weeks. The last and highest dosing step will be fed until the individual end of the study. Taking both safety and efficacy into account, the initial dose of allergens in the study powder as well as the respective up-dosings were determined on the basis of ED_05_ [17]. The target allergen doses for each study period were verified by analyzing the final study product. Table 1 summarizes the results obtained within this analysis.

**Table 1 Tab1:** Allergen amount in study product (amount of daily protein)

	Amount of protein daily [mg]			
	Peanut	Hazelnut	Hen’s egg	Cow´s milk
**Active group**				
**Dose 1 (V1–V2)**	1.7	1.9	1.8	2.0
**Dose 2 (V2–V3)**	8.4	10.0	9.0	10.0
**Dose 3 (V3–V4)**	39	44	42	45
**Dose 4 (V4–V5/V6)**	146	164	155	167
**Placebo group**				
**V1–V5/V6**	0	0	0	0

The sugar-free, rusk-like biscuit powder (3 g of powder/day using a measuring spoon) will be mixed with water, and optionally fruits, to a mash. The study product should be eaten on a daily basis throughout the study duration. The first feeding of the study product as well as every dose increase, each after 6 weeks, will be performed under medical supervision at the study center. In case of adverse events, the intervention may be individually modified according to investigator’s discretion.

In the placebo group, subjects consume daily a sugar-free rusk-like biscuit powder, without HE, CM, PN, and HN, analogously to the intervention group. The first and next dosing step feedings of the placebo study product will also be performed under medical supervision at the study site to maintain the blinding.

The first weaning food (e.g., vegetables) should have been successfully introduced for at least 1 week before feeding of the active/placebo product. Mothers will be encouraged to continue with breastfeeding while introducing weaning foods. Parents of both groups will be advised to avoid HE, PN, and HN or their products in their child’s diet. If the subject is unable to consume the recommended amount of rusk like biscuit powder, i.e., in the frame of feeding difficulties when weaning foods are introduced, the investigator and study physician may adjust the amount or dosing regimen within the patient’s diet. Non-compliance is defined as a repeated event of insufficient consumption of the intervention product, i.e., less than 3 times/week for 3 weeks (either during 3 consecutive weeks or three repeated events of 1 week). All participants may continue their usual medications, also those taken for any concomitant diseases, including wheezing and eczema, throughout the study. All subjects who will undergo an OFC at visit 6 will be advised to discontinue oral antihistamines 3–5 days before this procedure.

### Primary endpoint

The primary endpoint is the occurrence of IgE-mediated food allergy determined with level 1 or 2 to at least one of the four foods (HE, CM, PN or HN) after 6–8 months of intervention (at around 1 year of age).

The diagnosis of food allergy will be determined according to the following levels:
Level 1: A positive oral food challenge at around one year of age in a child with allergen-specific IgE > 0.1 kU/l or skin prick test (SPT) wheel size > 3 mm.Level 2: A systemic reaction with objective symptoms upon accidental exposure in a child with specific IgE to one of the four intervention foods > 0.1 kU/l or SPT wheel size > 3 mm.Level 3: Allergen- or allergen component-specific IgE above the 90% predicted probability for this individual food [18, 19].

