### Randomization, allocation concealment, and blinding

After enrolment, participants will be randomly assigned to the active or placebo group in a 2:1 manner. The randomization will be prepared by the trial statistician and will be implemented within the REDCap (Research Electronic Data Capture) database system by the data manager. The randomization will include a technical stratification regarding singleton/twin status. Singletons will be assigned to the treatment groups by simple randomization in a 2:1 manner (active: placebo). Twins will also be randomly assigned to the treatment groups in a 2:1 manner (active: placebo); however, twins will be randomized together, i.e., each pair will be randomized into the same treatment group. Thus, the ratio of 2:1 will be implemented on the pair-level. In addition, the randomization of twins will be blocked (block length: 3 pairs (i.e., 6 subjects)) due to the low number of twins expected in this study. The rationale for randomizing twins into the same treatment group is the difficulty for parents to ensure the strict separation of the daily (blinded) feeding products to their infants over the course of 6–8 months. Study investigators, all involved study staff, and the parents of the participants are blinded to treatment. Allocation of subjects will be performed concealed (i.e., without knowledge of group allocation) by authorized site personnel using REDCap where each participant will be allocated to one out of fifteen kit codes for the interventional product (10 codes active, 5 codes placebo). The product will be labeled with the kit codes by staff, which is unblinded, but not otherwise involved in the study.

In general, unblinding per subject will be performed at the individual end of the study (if the patients are sensitized to HE, CM, PN, or HN at V5, they are instructed to continue consuming the study product until V6 takes place.) In case of serious allergic reactions suspected to be related to the study intervention, unblinding should be performed on the decision of the investigator. In order to ensure the unblinding process, emergency envelopes, providing information on the individual interventional group the subject is assigned to, are stored at the study center. Once unblinding has been performed, it will be documented in the source data, reported to the principal investigator and will result in the subjects’ early discontinuation of intervention.

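### Level 2 counts only accidental exposure, so a sensitised active-arm infant who reacts systemically to the study product and is never challenged is not a primary event; the omission can only favour active

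*Protocol article*

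**What the plan says.** The Methods of the protocol article, under the heading Primary endpoint, define the outcome as follows: "The primary endpoint is the occurrence of IgE-mediated food allergy determined with level 1 or 2 to at least one of the four foods". The two levels that count are:

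- "Level 1: A positive oral food challenge at around one year of age in a child with allergen-specific IgE" above 0.1 kU/l or a skin prick wheal above 3 mm.
- "Level 2: A systemic reaction with objective symptoms upon accidental exposure in a child with specific IgE to one of the four intervention foods" above the same thresholds.

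Level 3, which rests on IgE and needs no challenge, is outside the primary endpoint.

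Methods, Intervention, on the product: "The study product should be eaten on a daily basis throughout the study duration". On the comparator: "In the placebo group, subjects consume daily a sugar-free rusk-like biscuit powder, without HE, CM, PN, and HN".

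Methods, Randomization, allocation concealment, and blinding: the investigator may unblind after a serious allergic reaction suspected to come from the intervention, and unblinding leads to "early discontinuation of intervention". Methods, Study procedures: infants sensitised at V5 are invited to a challenge at V6, and those who stop or deviate are encouraged to keep attending. Methods, Statistical analysis: missing values are not imputed.

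**The concern.** Level 2 exists so that a clear clinical reaction counts even without a challenge. As worded, it does this unequally. A placebo infant who reacts systemically to egg eaten by accident is an event without a challenge. An active infant who has the same reaction to egg in the product is an event only if later challenged with a positive result. Placebo infants cannot have the uncounted reaction, because their product holds none of the four foods.

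The article keeps the two kinds of exposure apart elsewhere: in Study procedures, the instruction to parents on reporting immediate reactions names the study product and other food exposure separately. Level 2 carries over only part of the second.

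Such reactions are foreseeable. By the article's account, about half of infants with eczema become sensitised and about a third develop clinical allergy, and the product is started without prior sensitisation screening. At stake is the trial's only confirmatory comparison.

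**Working it through.** **1. The plan's own figure.** Inputs (Sample size calculation): 33% placebo, 10% active, 40 and 80 analysed, two-sided 5% chi-squared test.

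- Pooled rate = (40 × 0.33 + 80 × 0.10)/120 = 0.1767.
- SE under the null = √(0.1767 × 0.8233 × (1/40 + 1/80)) = 0.0739.
- SE under the alternative = √(0.33 × 0.67/40 + 0.10 × 0.90/80) = 0.0816.
- Power = Φ((0.23 − 1.96 × 0.0739)/0.0816) = Φ(1.045) = 85.2%.
- Randomised = 120/0.8 = 150.

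The stated design reproduces.

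**2. Which infants count.**

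| Sensitised infant | V6 challenge | Primary event? |
|---|---|---|
| Either arm, systemic reaction to accidental exposure | not done | yes, Level 2 |
| Active, systemic reaction to product | done, positive | yes, Level 1 |
| Active, systemic reaction to product | not done | no |
| Placebo, allergic reaction to one of the four foods in product | – | cannot occur |

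**3. Direction.** Let p be the true allergy rate and f the share of allergic active infants who react to the product and are never challenged. The observed active rate is p(1 − f)/(1 − pf) if they are missing, and p(1 − f) if they are non-events (other dropout aside). Both are below p for any f > 0. The placebo rate is unaffected.

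**4. Size with no true effect.** Assumptions: p = 0.33 in both arms, 100/50 randomised, 10% other dropout, reactors missing, uncorrected chi-squared test, by simulation. The article gives no value for f, so a range is shown.

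| f | Active infants lost (33 × f) | Active rate reads | Rejection rate |
|---|---|---|---|
| 0 | 0 | 33.0% | 5.0% |
| 5% | 1.7 | 31.9% | 5.3% |
| 10% | 3.3 | 30.7% | 6.1% |
| 20% | 6.6 | 28.3% | 9% |
| 30% | 9.9 | 25.6% | 15% |

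Nearly all the excess falls on the side of active. Exact enumeration at 40 versus 80 analysed gives a 2.6% chance of a significant result favouring active at f = 0, 4.7% at 10% and 13.5% at 30%. On the same basis at f = 30%, scoring these infants as non-events makes the active rate read 23.1% and raises that chance to 22.2%.

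**5. Plausible ceiling for f.** Total active loss is 33f + 0.10 × (100 − 33f). Setting this to the planned 20 gives 29.7f = 10, so f = 34%. Higher values would exceed the plan's own dropout allowance.

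**6. At the planned result.** 8/80 versus 13/40 gives p = 0.002. Adding k uncounted active reactors as events: k = 4 (12/84) gives p = 0.018, k = 6 (14/86) p = 0.039, and k = 7 (15/87) p = 0.054. Significance is lost only if 7 of 15 allergic active infants went unchallenged.

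**7. Effect of the remedy.** Under the assumptions of step 4, counting the unchallenged reactors as events returns the rejection rate to about 5%. The active rate reads slightly high because reactors escape other dropout: at f = 30%, 0.33 × (0.9 × 0.7 + 0.3)/(0.9 × (1 − 0.099) + 0.099) = 0.3069/0.9099 = 33.7%.

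**The case against.** The strongest reply is that a product reactor stays eligible for Level 1. Unblinding is discretionary, is reserved for serious reactions, and ends the intervention rather than follow-up. Everyone sensitised at V5 is invited to V6. A reader might infer that reacting families will decline the challenge and drop out, but the article says neither. This stands: it is why f is unknown and why the small-loss rows matter. It does not close the gap, since attendance is encouraged rather than assured and an invitation can be refused.

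Second, the article is abridged, and protocol version 4.0 may define Level 2 more widely or say how an unchallenged sensitised infant is scored. That is possible. But the published definition states a restriction, and both ways of scoring err towards active.

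Third, other planned outputs would help reveal the problem: the Level 1, 2 or 3 secondary endpoint, immediate-type symptoms, and adverse events by group. They are exploratory or descriptive, and none turns an unchallenged product reaction into a primary event.

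Fourth, counting product reactions opens an event route that placebo infants do not have, and a reaction early in the study may not reflect allergy at around one year. Both are fair. They are the reason a V6 challenge result should take precedence.

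**Conclusion.** The gap is real on the published wording and should be fixed. It omits events from the active arm only, so it can only favour active. Its size cannot be derived from the article: with no true effect, the rejection rate runs from about 5.3% at a 5% loss to about 15% at a 30% loss. These figures assume 33% allergy in both arms and 10% other dropout. The planned effect would survive all but a large loss; a smaller or absent effect is more exposed.

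Three stronger readings are not supported.

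- **The per-protocol analysis shares the bias.** The article says "Non-compliance is defined as a repeated event of insufficient consumption of the intervention product, i.e., less than 3 times/week for 3 weeks" but does not define the per-protocol set or say that this rule decides membership.
- **Deliberate cow's milk feeding adds to the bias.** The advice is "Parents of both groups will be advised to avoid HE, PN, and HN or their products", so milk may be fed in either arm and creates no arm-specific omission.
- **Level 2 lets the reacting food differ from the sensitising food.** This strains a definition that serves an endpoint of allergy to at least one named food, and it would not act on one arm alone.

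**What to change.** Extend Level 2 to systemic reactions with objective symptoms on any exposure to the four foods, including the study product. Keep the same sensitisation criterion, adjudicate blind to arm, and let a V6 challenge result take precedence where one exists. Count product reactions for the any-food endpoint only, because the product mixes all four foods. Say how a sensitised infant without a challenge is scored, and whether the V1 blood sample may establish sensitisation when V5 was missed. The amendment must be decided blind to accumulated outcomes by arm.

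That condition may no longer be attainable. Infants are unblinded at their individual end of study, and the first was randomised in February 2020. Six to eight months later is August to October 2020, before protocol version 4.0 of April 2021. If some outcomes are already unblinded, keep the current definition as primary and prespecify a sensitivity analysis that counts unchallenged, sensitised product reactors as events, reporting their number by arm.

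The cost is an amendment or an analysis-plan entry plus adjudication of reactions the trial already records; no new visits are needed. The downside is a slight tilt against active, because the added route is open only to that arm, and product reactions cannot be assigned to one food.
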